### Sample size calculation

The main scientific hypothesis is that the possibility of teledermatology in general practice will reduce the number of referrals to a dermatologist by 15% in the intervention group. The statistical null hypothesis is a reduction of 0%, the alternative is a reduction > 0%. The basis of the sample size calculation is an assumed reduction of 15%.

A mean of 120 referrals to dermatologists per year and GP is assumed. In 2015, 40% of AOK-insured patients were enrolled in the HzV [28, 29]. Thus, for the subgroup of AOK patients, 48 dermatological referrals per year and GP practice are to be expected in the control population during the 1-year intervention phase of the study. A Poisson distribution of the referrals for each GP team is assumed. Furthermore, a type I error of 5% (two-sided) and a type II error of 20% are defined. These assumptions lead to a calculation of 36 analyzable GP teams (with, on average, 48 referrals per year and GP practice each) per study arm. On the patient level, this amounts to 1728 patients with the indication for a referral to a dermatologist in total. A 15% reduction equals 260 referrals in total. A 30% dropout buffer is taken into account. The final sample size calculation amounts to 2400 patients with a reduction of 360 referrals.

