### Data analysis (t_2_ in Fig. 1)

The pooled routine dataset is sent from AOK to the aQua institute. The aQua institute selects, filters and anonymizes the data. Lastly, the aQua institute delivers the anonymized patient dataset to the Institute for Clinical Epidemiology and Applied Biometry (IKEaB) for statistical analysis. All of these transfers use a secure, encrypted protocol and are authenticated. The relevant data sources are subject to extensive quality management processes. To secure data protection of interview and questionnaire data as well as process data from the KSYOS system, the Tübingen University Hospital’s (UKT) data protection agency is involved. They are independent from the sponsor.

For the primary outcome, Poisson regression is chosen as an analysis tool. To consider practice size and patient load, the number of practice KV bills during the intervention phase is applied as an offset. The dichotomous factor “study arm” is applied for the calculation. The GPs are the unit of observation. For both study arms, separate confidence intervals are created for the number of referrals per KV bill.

For the sample size calculation, a simple *t* test was used. In contrast to the sample size calculation, the statistical analysis will use a more complex method (Poisson regression). This is expected to lead to an increased power of the study, because the offset “total number of KV bills during intervention” explains parts of the variability between GP teams. Study power should thus be over 80%. Primary analysis will be calculated as a Poisson regression with a significance level of 5% (two-sided). Analogous methods will be applied to secondary outcomes (see later). However, the interpretation of local significances is not designed to be strictly confirmatory. Due to the multitude of secondary parameters lacking hierarchical structure, a correction for multiple tests is unrealistic. Descriptive analyses are performed following scaling and observed data distribution.

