Another challenge for the implementation of telemedicine in German primary care is the heterogeneity of practices. Basically each aspect of daily work (team structure, patient management software, size of the practice, practice organization) is different between practices [33]. For example, about 235 different digital patient data management systems exist in Germany [34]. In 2017, German law enforced the implementation of a generic patient data interface within 2 years [35]. Using such an interface is currently the only way to export patient data to third-party solutions, like the KSYOS teledermatology system. Nevertheless, there still are some PMSs that do not support such an interface or ask for licensing and support fees. The GP may use the teledermatology nevertheless by manually importing and exporting data, but that might prove too time-consuming for daily practice. The consequence might be that the GP drops out of the study.

To ensure the intervention’s success, GPs must be allowed to choose their own way of implementing the intervention in their practice. Thus, it is allowed for GPs to delegate parts of the teledermatology procedure (e.g., photography of the skin lesions) to practice staff. This way, the acceptance of the intervention hopefully increases, thus resulting in more realistic and reliable results.

In order to grasp the multitude of different perspectives, a mixed-methods evaluation was designed. We hope to identify relevant barriers and enablers for the implementation of sustainable teledermatology in routine general practice. If we succeed, the TeleDerm study could be a milestone in the implementation of telemedicine in general and teledermatology in particular in Germany.

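### The KV-bill offset is credited with raising power, but the gain is real only if referrals rise more than about half in proportion to bills, and the article does not show that they do

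*Protocol article*

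**What the plan says.** In the article's section Data analysis, the primary analysis is a Poisson regression with study arm as the only factor, the GP as unit of observation, and a size term: "the number of practice KV bills during the intervention phase is applied as an offset". The section recalls that the sample size came from a t test and then compares the two methods. Of the Poisson model it says "This is expected to lead to an increased power of the study, because the offset" (total KV bills) "explains parts of the variability between GP teams", and concludes that power should exceed 80%. No condition is attached.

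The section Sample size calculation supplies the planning inputs: "a type I error of 5% (two-sided) and a type II error of 20% are defined", a 15% reduction, "48 dermatological referrals per year and GP practice are to be expected in the control population", and "A Poisson distribution of the referrals for each GP team is assumed". It arrives at 36 analysable teams per arm. The Discussion adds: "Basically each aspect of daily work (team structure, patient management software, size of the practice, practice organization) is different between practices".

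**The concern.** An offset is a size term whose coefficient is set to 1 and not estimated. It assumes that a practice with twice the bills makes twice the referrals. If that is roughly true, dividing by bills removes noise. If referrals rise much more slowly than bills, dividing by bills puts the spread of bills into the outcome and makes the comparison noisier than with no size term.

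The article reports nothing on how referrals relate to bills. There is also a reason to doubt strict proportionality: the study population is AOK-insured adults enrolled in the HzV, while the offset is the practice's KV bills. How far the two move together depends on each practice's mix of patients.

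At stake is the power claim for the confirmatory test. Depending on the variance estimate, a low slope would show either as power below the t test or as a test that rejects too often.

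**Working it through.** **Inputs from the article.** Two-sided 5%, power 80%, control mean 48, intervention mean 0.85 × 48 = 40.8, difference 7.2, 36 practices per arm, Poisson counts; arm-only Poisson model with KV bills as offset; the t test as comparator.

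**Not in the article, so assumed.** The slope b of log referrals on log bills, the SD s of log bills, and the between-practice SD. There is no county effect below.

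**1. The plan's own figure.** With Poisson SD √48 = 6.93, n = 2(1.96 + 0.842)² × 48 / 7.2² = 14.5, so 15 per arm, not 36. The stated 36 gives 80% t-test power only if the practice SD is 10.75, an extra-Poisson CV of √(10.75² − 48)/48 = 0.171, or a log-variance of ln(1 + 0.171²) = 0.0289. I use this back-solved SD because it is the only between-practice spread consistent with 36.

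**2. Model-based standard error.** In an arm-only Poisson model the fitted arm totals equal the observed totals Y1 and Y0, so SE(log RR) = √(1/Y1 + 1/Y0) whatever the offset. Here it is √(1/1468.8 + 1/1728) = 0.0355. One simulated data set fitted both ways gave 0.0356 with and without the offset, while the estimate moved from −0.267 to −0.149.

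**3. True scatter.** Let r be the log-variance between practices not related to bills.
- No size term: b²s² + r
- Offset: (1 − b)²s² + r
- Estimated slope: r

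Offset minus no size term is (1 − 2b)s², so break-even is b = 0.5 to first order.

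**4. Power.** Hold b²s² + r at 0.0289. Then SE² ≈ (2/36) × log-variance + 0.0355², and power ≈ Φ(0.1625/SE − 1.96), with 0.1625 = −ln 0.85. Example, s = 0.3, b = 0.25: r = 0.0289 − 0.0056 = 0.0233. With the offset the log-variance is 0.5625 × 0.09 + 0.0233 = 0.0739, so SE = √(0.00411 + 0.00126) = 0.073 and power is 60%. With no size term SE = √(0.00161 + 0.00126) = 0.0535 and power is 86%.

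| s | b | Formula: none / offset / estimated slope | Simulated, dispersion-corrected: t test / offset / estimated slope |
|---|---|---|---|
| 0.3 | 0.25 | 86 / 60 / 89% | 85 / 59 / 89% |
| 0.3 | 0.5 | 86 / 86 / 98% | 83* / 82 / 97% |
| 0.5 | 0.34 | 86 / 48 / 99.6% | 85 / 45 / 99% |
| 0.2 | 0.85 | 86 / 99.4 / 99.6% | 85 / 99.6 / 99.6% |

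*Poisson model without size term, which with a dispersion correction is practically the t test. Simulated figures differ by a few points between runs. The t test shows 85% and not 80% because the SD in the intervention arm is below 10.75: √(40.8 + (0.171 × 40.8)²) ≈ 9.5.

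**5. Type I error with the unscaled Poisson SE.** Under no effect that SE is √(2/1728) = 0.0340. At s = 0.3, b = 0.25 the true SE with the offset is √(0.00411 + 0.00116) = 0.0726, so the 1.96 limit acts as 1.96 × 0.0340/0.0726 = 0.92 and type I error is about 36% (simulated 38%). Without a size term it is already about 20% (limit 1.27). With an estimated slope it is about 18%. At s = 0.5, b = 0.34, simulation gave 47% with the offset and 5% with an estimated slope.

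**6. Two extremes with no other extra-Poisson variation, bill CV 0.4, unscaled SE.**
- b = 0 (every team with mean 48, one reading of the Poisson assumption): there is no extra variability to explain. The offset lowers the rejection rate from 99.6% to 83% and raises type I error from 5% to 51%.
- b = 1 (strict proportionality): the t test has 36% power and Poisson with offset 99.5%, with type I error 5%.

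**The case against.** The strongest defence is that an unchanged model-based standard error says nothing about power. Power depends on the real scatter of the estimate, and where referrals track bills the offset reduces it. That is the case an offset for practice size is meant for, and the gain over the t test is then large (85% to 99.6%, or 36% to 99.5%). This stands. A reader might infer from the standard-error identity that the offset explains nothing and that the stated reason is false; the calculations do not support that.

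Second, the power losses appear only with a dispersion-corrected standard error, which the article does not name. With the unscaled one, rejection rates under the 15% reduction stay at or above about 80%. That is correct, but it does not rescue the claim: in the low-slope settings those rates come with type I error of 38% and 47%, so they are not valid power.

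Third, b, the bill spread and the SD of 10.75 are assumptions. This also stands. It might be tempting to say that the offset must lose power once s exceeds about 0.34 (0.17/0.5), but that follows only from the back-solved SD.

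Fourth, an offset is the standard model for a rate per bill, which the article wants to report. That rate can still be reported by arm without fixing the slope in the test.

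**Conclusion.** The point holds as a statement about an unsupported condition. The article presents a power gain as unconditional when it depends on a slope above about 0.5 that is nowhere documented. With 36 practices per arm and an SD of 10.75, the offset takes power from 85% to anywhere between 45% and 99.6% over the settings tried. With the plain Poisson standard error the same loss would go unseen and would inflate type I error.

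The documents do not show that power is below 80%, nor that the offset is harmful in this trial. They show only that the article has no basis for claiming the gain. An estimated slope matched or beat the offset in every setting of the table, so this is a cheap improvement to the primary analysis and more than a wording matter. It should be made.

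**What to change.** Let the coefficient of practice size be estimated: either keep the offset and add log KV bills as a covariate, or replace the offset by that covariate. Both give the same arm effect. Keep referrals per KV bill, with confidence intervals, as the descriptive rate by arm.

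Restate the power sentence as conditional on referrals tracking bills, and do not claim power above the t-test figure on the ground of the offset alone.

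The cost is one degree of freedom and a change of reading: the rate ratio is then at equal practice size instead of per bill. If referrals were exactly proportional to bills, the offset would be marginally more efficient. No new data are needed. The estimated slope does not by itself correct the plain Poisson standard error for variation unrelated to bills (type I error still about 18% in one setting above); that is a separate matter.

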## Methods

### Study design and setting

The study is planned as a cluster-randomized controlled confirmatory study, where a county is regarded as one cluster. The main scientific hypothesis is that the possibility of store-and-forward teledermatology in GP practices is going to reduce GP referrals to dermatologists by at least 15%. This protocol follows the Guidance of Standard Protocol Items: Recommendations for Interventional Trials (SPIRIT) 2013 Statement [22]. It includes the schedule of enrolment and relevant assessments (Fig. 1) using the SPIRIT figure template. A SPIRIT checklist is provided in Additional file 1.

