**Fig. 2 Fig2:**
[figure not shown]
Project timeline of the 3-year project. GP general practitioner

The cluster level “county” is randomized into four intervention and four control counties. In the intervention counties, data from non-participating HzV practices will serve as an internal control group at the cluster level “practice”. At the cluster level “patient”, data from nonparticipating patients are used as a second internal control group. No blinding is applied to any level of the trial. Figure 3 shows both study arms and an overview of the different cluster levels.

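### The claim of over 80% power leaves out variation between the eight randomised counties; for a valid county-level test it holds only if that residual variation is small (CV up to about 0.046, roughly 0.03 to 0.065 across variants)

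*Protocol article*

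**What the plan says.** Under Study design and setting, the article states: "The study is planned as a cluster-randomized controlled confirmatory study, where a county is regarded as one cluster". Under Study design, the county level "is randomized into four intervention and four control counties".

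The Sample size calculation section works at practice level. "A mean of 120 referrals to dermatologists per year and GP is assumed"; with 40% applied for the AOK subgroup, "48 dermatological referrals per year and GP practice are to be expected in the control population". "The basis of the sample size calculation is an assumed reduction of 15" per cent, and "a type I error of 5% (two-sided) and a type II error of 20% are defined". On the variance, "A Poisson distribution of the referrals for each GP team is assumed". The result is 36 analysable GP teams per arm, with a 30% buffer for dropout.

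The Data analysis section says that the calculation was a simple t test. The primary model is a Poisson regression with study arm as factor, the number of KV bills as offset and GPs as units of observation. Because the offset is expected to explain part of the variability between GP teams, the section concludes: "Study power should thus be over 80" per cent. It adds that analyses at GP-team level, including those on AOK insurance data, carry no cluster adjustment, on the ground that each team contributes one measurement.

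**The concern.** Power in a cluster-randomised trial depends on how much the randomised units differ and how many there are. Here there are eight, and the calculation contains no between-county variance, intracluster correlation, design effect or small-sample allowance. The one reason given for exceeding 80% concerns practices, not counties.

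The trial calls itself confirmatory. If the power figure is taken at face value, a null result would be read as evidence against a 15% reduction. The design supports that reading only if residual differences between counties are small.

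**Working it through.** **Inputs from the article.** 4 + 4 counties; 36 practices per arm; control mean 48 referrals per practice-year; 15% reduction, so rate ratio 0.85 and difference 0.15 × 48 = 7.2; two-sided 5%; target power 80%; Poisson counts.

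**Assumptions.** Practices are spread evenly (9 per county). k is the coefficient of variation of the true referral rate per bill between counties, remaining after matching and offset. The article gives no value for k.

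**1. The plan's own figure.** n per arm = 2s²(1.960 + 0.842)² / 7.2².
- With s² = 48 (Poisson at the stated mean): 14.5, so 15 by the normal formula, or 16 by the t test (15.6). With 36 per arm, power would be 99%.
- With s² = 120 (SD 10.95): 36.3. Power at 36 is 79.6% (normal) or 78.5% (t test).

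So 36 does not follow from the stated Poisson mean of 48. It is nearly matched by an SD of about 10.95. The article does not say where 36 comes from.

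**2. County-level test.**

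var(log RR) = 1/(36 × 48) + 1/(36 × 48 × 0.85) + 2k²/4 = 0.000579 + 0.000681 + k²/2

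Effect = −ln 0.85 = 0.1625. Noncentrality = 0.1625/SE. Noncentral t with 6 df, critical value 2.447.

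| k | variance | SE | noncentrality | power |
|---|---|---|---|---|
| 0 | 0.00126 | 0.0355 | 4.58 | 97% |
| 0.05 | 0.00251 | 0.0501 | 3.24 | 77% |
| 0.10 | 0.00626 | 0.0791 | 2.05 | 41% |
| 0.15 | 0.01251 | 0.1118 | 1.45 | 23% |

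Solving for 80% gives k = 0.046.

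**3. How firm is 0.046?** The k at which power is 80%, under variants:
- normal instead of t critical value: 0.065
- 50 practices per arm: 0.053
- 25 practices per arm: 0.032
- negligible Poisson noise in the control arm (many control practices in the routine data): 0.057

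**4. More practices in the same counties.** With unlimited practices the variance tends to k²/2, and power is 80% at k = 0.068. At k = 0.05, 42 practices per arm give 80%, 50 give 83%, and the limit is 97%. At k = 0.10 the limit is 49%, and at 0.15 it is 25%.

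**5. Extra-Poisson variation between practices.** If the SD of 10.95 remained in both arms after the offset, then at k = 0:

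variance = 120/(36 × 48²) + 120/(36 × 40.8²) = 0.00345; SE 0.0587; noncentrality 2.77; power 64%.

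If the SD falls in proportion to the mean, power is 71%. In neither case does any k give 80%.

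**6. The planned model.** In simulation (20,000 runs, pure Poisson within county), Poisson regression without a county term rejected a true null in about 10% of runs at k = 0.03, 17% at 0.05, 39–40% at 0.10 and 55% at 0.15. It still rejected in 97% of runs at k = 0.05 and 88% at 0.10 when the reduction was 15%, but not at the stated 5% level.

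**The case against.** **k is not in the documents, and the counties are matched.** Both are true. The counties were selected for similarity, and the Table 1 indicators are to be used for matching and randomisation, so residual k may be small. A reader might infer that the trial is shown to be underpowered, for instance at 41%. The documents do not support that, because the values at k = 0.10 and above are scenarios. Equally, no residual k is stated, so over 80% is not supported either. Matching is no free gain if the analysis is paired: with four pairs and 3 df, power at k = 0 falls to 85%.

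**The offset argument has merit.** A reader might say that Poisson counts leave no variability between practices for an offset to explain. That goes too far. The article assumes Poisson counts for each team around 48 on average, so team means may differ with practice size, and an offset can recover that. What stands is that it does not address county differences in referrals per bill.

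**More practices could help.** A reader might infer that recruiting within the same counties cannot restore power. That is wrong for k below about 0.07 (step 4) and right above it. The 30% buffer is set aside for dropout and practice heterogeneity, so it cannot be counted on for this.

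**The threshold is fragile.** This stands. It rests on 36 pure-Poisson practices in each arm, while control data come from routine records and need not be limited to 36 practices. Hence the range in step 3. Nor does k = 0.05 mean that any two counties differ by less than 5%; k is a standard deviation relative to the mean.

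**The planned model would still reject often.** It would, but by exceeding its 5% type I error (step 6). That is not power at the stated level.

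**Internal controls allow cluster effects to be examined** (Strengths and limitations). They enter neither the primary model nor the power calculation.

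**Conclusion.** The claim of over 80% power is not supported as stated. The calculation omits between-county variance and the small number of randomised units, and the offset does not supply either. For a valid county-level test, 80% is reached only if residual k is at most about 0.046 under the plan's own Poisson assumption, or roughly 0.03 to 0.065 across reasonable variants. Pure Poisson variation within county is close to the favourable end; extra variation between practices lowers power, to about 64% even at k = 0 if the SD of 10.95 persists after the offset.

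The conclusion rests on an assumed k, an even spread of practices, and a test that respects county randomisation. It does not establish the trial's actual power, which could exceed 80% if the matched counties are very alike.

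**What to change.** - Withdraw the statement of over 80% and the offset justification for it.
- State power for four against four counties as a table over k, with the degrees of freedom used. Estimate k from county referral rates per bill in past AOK data.
- State what matching is assumed to do to k and to the degrees of freedom, what variation between practices is assumed beyond Poisson, and how 36 per arm was obtained.
- Say in advance what a null result can support at the power so obtained. If k proves to be near 0.10, it should not be read as evidence against a 15% reduction.

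The cost is rewording two sections and one query of past AOK data. The stated power will probably look less favourable. This correction requires no extra counties, practices or data collection, and it remains possible although enrolment has begun.

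Tabulating power for a county-level test also makes visible that the primary model has no county term. The analysis and the power statement should refer to the same test.

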### Strengths and limitations

The heterogeneity of GP practices, as stated earlier, is one of the major challenges of the study. We expect this to have an impact on the activity of the referring GPs. Therefore, we will recruit 30% more GPs than needed for statistical power to suffice. The internal control group allows us to examine cluster effects.

During the run-in phase of 6 months, first experiences with the technical implementation and the application of the teledermatology system in daily practice are made. This information will allow adjustments of the implementation processes in the GP practices. Also, we aim to address possible data safety concerns on all sides (GPs, patients, AOK). Experiences collected during run-in will be used to constantly inform and improve the ongoing implementation process.

An advantage of this study is that GP participants need little extra training. The intervention is tailored and very close to the reality of routine general practice in Germany. This, with the gained experiences from the study, will help to facilitate a bigger roll-out of teledermatology in German general practice in the future. To enable and plan a large-scale roll-out is a prerequisite for the funding for this study.

Our design allows us to collect information that has an impact from the implementation into routine care such as acceptance among patients and GPs. If the study succeeds, it will be the first teledermatology store-and-forward project to actually pass the barrier from a research project into daily practice, thus reaching new horizons for the much anticipated advance of eHealth in Germany.

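### The primary Poisson regression has no allowance for variance above the mean, so any difference in referral rates between practices that the bill offset leaves behind makes its standard error too small, even with no county effect

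*Protocol article*

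**What the plan says.** All references are to the protocol article.

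- **Model (Data analysis).** "Primary analysis will be calculated as a Poisson regression with a significance level of 5% (two-sided"). The only explanatory factor is the arm: "The dichotomous factor “study arm” is applied for the calculation". Practice size enters through the offset: "the number of practice KV bills during the intervention phase is applied as an offset". "The GPs are the unit of observation". Per arm, "separate confidence intervals are created for the number of referrals per KV bill".
- **Distribution (Sample size calculation).** "A Poisson distribution of the referrals for each GP team is assumed".
- **Effect of the offset (Data analysis).** The total number of bills "explains parts of the variability between GP teams". From this the article expects more power than the t test behind its sample size, and so more than 80%.
- **Heterogeneity (Discussion; Strengths and limitations).** The Discussion says that practices differ in practically every aspect of daily work. The limitations section adds: "The heterogeneity of GP practices, as stated earlier, is one of the major challenges of the study".
- **What is not named.** The primary model has no dispersion parameter, negative binomial form, practice effect or robust variance. Generalized estimating equations are mentioned for secondary outcomes only. In that same paragraph, GP-level models are to run without cluster adjustment because each team is measured once.

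**The concern.** A plain Poisson regression sets the variance of each count equal to its mean. If practices keep different underlying referral rates after allowing for their number of bills, the counts vary more than that, and the reported standard error leaves the excess out. Measuring each team once removes repeated-measures correlation. It does not make the teams' rates equal. Nor does it help that each team's own count may be Poisson: teams with different rates still give a variance above the mean across teams.

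This is separate from the randomisation of whole counties, because it arises between practices within one county. At stake are the nominal 5% level of the single confirmatory test and the coverage of the per-arm intervals. Other practice-level counts from the routine data, analysed by analogous methods, share the problem. The consequence there is smaller, because the article does not treat secondary tests as strictly confirmatory.

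**Working it through.** **Inputs from the document.** Control mean 48 referrals per practice and year; 15% reduction, so 40.8 and a difference of 7.2; 36 teams per arm; two-sided 5%; power 80%; t test for the sample size. **Assumed:** the residual between-practice CV after the offset, varied from 0 to 0.30, because the document gives no SD. County variance is set to zero throughout.

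**1. The plan's own figure.** With pure Poisson counts the SD is √48 = 6.93. The normal formula gives n = 2 × (1.96 + 0.842)² × 48 / 7.2² ≈ 14.5, so 15 per arm; the exact t test needs 16. At 36 per arm the power would be about 99%. The stated 36 is therefore not reproduced under the Poisson assumption.

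If 36 per arm came from a t test at 80% power on 48 versus 40.8, the SD would be 10.75. That is a dispersion of 10.75² / 48 ≈ 2.41 and a between-practice CV of √((115.6 − 48) / 48²) = 0.171. This is only indirect evidence:
- The SD is not stated.
- A mean of 19.2 (40% of 48) with pure Poisson counts gives 37 per arm.
- The article's total of 1728 equals 36 × 48, which fits 36 practices in one arm, or 18 per arm (pure Poisson power about 86 to 88%).

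**2. What the model reports.** With arm and offset only, the Poisson standard error of the log rate ratio is √(1/E1 + 1/E0), where E1 and E0 are the total referrals per arm. Between-practice scatter does not enter it.

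**3. What the standard error should be.** With residual CV c, the variance of a count is 48 + 48²c², so the dispersion is φ = 1 + 48c². The true standard error is √φ times the reported one. The true size of the nominal 5% test is 2 × [1 − Φ(1.96/√φ)], and interval coverage is one minus that. Power in the last column is for a 15% reduction under quasi-Poisson with a t reference.

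| Residual CV | φ | √φ (interval widening) | Type I error, plain Poisson | Power after correction |
|---|---|---|---|---|
| 0 | 1.00 | 1.00 | 5% | 99% |
| 0.05 | 1.12 | 1.06 | 6% | 99% |
| 0.10 | 1.48 | 1.22 | 11% | 96% |
| 0.15 | 2.08 | 1.44 | 17% | 89% |
| 0.20 | 2.92 | 1.71 | 25% | 77% |
| 0.30 | 5.32 | 2.31 | 39% | 53% |

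Simulation (gamma-Poisson counts, 36 equal-sized practices per arm, 40,000 runs per setting) agrees with the error column to within about one percentage point. There, quasi-Poisson with a t reference stays at about 5% throughout. With practice sizes that vary strongly, its simulated size is 5 to 7%.

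**4. What the offset does.** Take a total CV of 0.171, split between practice size (captured by the offset) and residual rate. Simulated type I error of plain Poisson with offset is about 21% if the offset captures none of the extra variance, 13% if half and 5% if all. In the half case, power for a 15% reduction is about 84% for the t test without offset and 94% for quasi-Poisson with offset.

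**The case against.** The strongest reply has four parts.

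- **The document never says that the variance exceeds the mean.** This is correct. A reader might infer from the remark about parts of the variability that extra-Poisson variation is conceded. But total variability includes Poisson sampling variation, so the remark does not state it outright. The heterogeneity passages are mainly about implementation, and one item they list, practice size, is what the offset addresses. What remains is that the article nowhere claims the offset removes all rate differences, and its model is valid only if it does.
- **The offset helps.** This stands. A reader might infer from the formula in step 2 of the working that the offset makes no difference, or that the sentence on power should go. Neither is supported. The reported standard error stays the same, but the true variance of the estimate falls, so the test is better calibrated, and a dispersion-corrected analysis gains power.
- **The size is unknown.** This also stands. A reader might take about 21% type I error and 79% coverage as this trial's figures. They follow from a dispersion of 2.4 back-solved from an ambiguous sample size statement, and they assume the offset absorbs none of the extra variance.
- **A condensed article may leave variance estimation to an analysis plan.** A plan not shown here may add a correction. But the article does not leave the primary model open: it gives family, factor, offset, unit and level, and none of these lets the variance exceed the mean.

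**Conclusion.** The point holds. As written, the primary test keeps its 5% level only if, after the bill offset, practices have no remaining differences in referral rate. The document gives no ground for that. The direction of the error is certain for any residual variation, and no county effect is needed.

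The size is conditional on an assumed CV: negligible near zero (6% at 0.05), about double the nominal level at 0.10, 25% at 0.20 and 39% at 0.30. Nominal 95% intervals then cover about 89%, 75% and 61% at 0.10, 0.20 and 0.30. These figures rest on 36 practices per arm, a mean of 48, independent practices and no county variance. The expectation of more than 80% power is reasonable at a residual CV of 0.15 or below, but not at 0.20 or above.

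**What to change.** In the Data analysis section, replace the plain Poisson regression by negative binomial regression, or by quasi-Poisson regression with the dispersion estimated from the data and a t reference. Choose one in advance. Keep the bill offset. Apply the same model to the per-arm intervals and to the other practice-level counts from the routine data.

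Keep the statement that the offset should raise power, but make the expectation of more than 80% conditional on the residual dispersion: about 96% at CV 0.10, 77% at 0.20 and 53% at 0.30, ignoring county effects.

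This is in addition to whatever is done about the eight randomised counties. A practice-level dispersion correction does not solve that.

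**Cost.** About a sentence of analysis wording and one of power wording, and no new data. Intervals become wider by the factor √φ in the table (1.2, 1.7 and 2.3 at CV 0.10, 0.20 and 0.30), with the loss of power just given. If the dispersion is truly 1, almost nothing is lost: the simulated size is about 5% and the power about 99% with either model.
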